## Abstract

**Background:**

Social anxiety disorder (SAD) is one of the most common mental disorders and causes subjective suffering and economic burden worldwide. Although effective treatments are available, a lot of cases go untreated. Internet-based self-help is a low-threshold and flexible treatment alternative for SAD. Various studies have already shown that internet-based self-help can be effective to reduce social phobic symptoms significantly. Most of the interventions tested include therapist support, whereas the role of peer support within internet-based self-help has not yet been fully understood. There is evidence suggesting that patients’ mutual exchange via integrated discussion forums can increase the efficacy of internet-based treatments. This study aims at investigating the added value of therapist-guided group support on the treatment outcome of internet-based self-help for SAD.

**Methods/design:**

The study is conducted as a randomized controlled trial. A total of 150 adults with a diagnosis of SAD are randomly assigned to either a waiting-list control group or one of the active conditions. The participants in the two active conditions use the same internet-based self-help program, either with individual support by a psychologist or therapist-guided group support. In the group guided condition, participants can communicate with each other via an integrated, protected discussion forum. Subjects are recruited via topic related websites and links; diagnostic status will be assessed with a telephone interview. The primary outcome variables are symptoms of SAD and diagnostic status after the intervention. Secondary endpoints are general symptomology, depression, quality of life, as well as the primary outcome variables 6 months later. Furthermore, process variables such as group processes, the change in symptoms and working alliance will be studied.

**Discussion:**

The results of this study should indicate whether group-guided support could enhance the efficacy of an internet-based self-help treatment for SAD. This novel treatment format, if shown effective, could represent a cost-effective option and could further be modified to treat other conditions, as well.

**Trial registration:**

ISRCTN75894275

## Background

Social anxiety disorder (SAD) is the third most common mental disorder after depression and alcohol dependency and is considered the single most prevalent anxiety disorder [1]. Characteristic for this disorder is the individual’s extreme fear that others might judge their behavior or physical symptoms as embarrassing [2]. The resulting high psychological suffering is furthermore the reason for high economic costs, such as low productivity at work, loss of working hours and under-qualification [1,3]. Without professional intervention, SAD tends to be a chronic condition [4]. Although effective psychological treatments and drug therapies are available [5], only a small proportion of those in need receive empirically-supported treatment [6]. This has several causes: In addition to factors that are valid for psychological disorders in general (such as fear of stigmatization, financial strains or the lack of qualified therapists in the immediate vicinity), the very nature of SAD can prevent individuals from seeking professional advice [1,7]. Against this backdrop, the current challenge is to make low-threshold, easily accessible treatment alternatives available to the high percentage of untreated individuals suffering from SAD. Internet-based treatments with their high level of anonymity and privacy and their easy accessibility seem to fit this profile.

Over recent years, the number of controlled trials evaluating Internet-based interventions has grown rapidly. By now, more than 100 controlled studies evaluating Internet-based treatments in the field of anxiety disorders, depression and other conditions have shown promising results [8-12]. Particularly in the treatment of anxiety disorders, independent replications have shown moderate to large effect sizes in comparison with control groups [9,10,12,13]. Most of this promising body of evidence comes from studies evaluating Internet-based guided self-help treatments, in which the presentation of a Web-based self-help program is combined with minimal but regular therapist contact via e-mail. Emerging evidence from meta-analyses (e.g. [12]) and from a reanalysis of data across trials [14] suggests a superiority of guided versus unguided self-help treatments in terms of efficacy, adherence to treatment and drop-out rates. However, therapist guidance does not seem to be needed in some disorders and under some conditions. For instance, in the treatment of SAD, good outcomes have been reported for unguided treatments if a proper diagnosis has been established [15,16]. SAD is among the most researched disorders in the field of internet-based treatments and it is a condition for which strong empirical support for the efficacy of Internet-based treatments exist [17]. However, there is room for optimizing and improving Internet-based treatments for SAD, as still a considerable number of patients do not benefit from or recover fully after an Internet-based treatment (e.g. [15]).

The general aim of this randomized controlled trial is to evaluate an internet-based treatment format which takes into account that in Internet-based treatments participants can also enter into an exchange with each other. Several prior studies on Internet-based treatments for SAD have included the possibility of peer support in moderated or unmoderated discussion forums with encouraging results (e.g. [15,18,19]). These forums are usually conceptualized and used as an additional option complementing the main treatment components such as the web-based self-help guide and individual therapist guidance. There is some initial evidence across studies that the additional peer support might increase the benefits of Internet treatments for SAD. For instance, Titov and colleagues could improve small within-group effect sizes for an unguided Internet-based self-help treatment for SAD [20] by adding a clinician-moderated online discussion forum [18]. Another study found comparable effects for an Internet-based guided self-help program for SAD and the same self-help guide delivered in the form of bibliotherapy with no therapist support but with access to an online discussion forum [19]. The use of an online discussion alone, without self-help guide, does not seem to lead to substantial changes in social anxiety [21].

Our own experience with integrated discussion forums is that many participants value the possibility to share information and experiences with other participants as one of the most helpful elements of the whole treatment package [22,23]. Moreover, qualitative analysis of the content of the discussions in our forums showed that therapeutic mechanisms of change, that are known from research on group psychotherapies, may come into play (e.g., normalization, altruism, instillation of hope, development of socializing techniques, interpersonal learning, imitative behavior, cohesiveness [24]). But there are also problems related to the use of discussion forums in Internet-based treatments. A practical problem is that participants usually do not start exactly at the same time with such treatments, they are therefore at different points in the treatment, and they may have different issues to discuss. Another problem is that while usually all participants read the messages in the discussion forums, only about half of them also post their own messages [15].

Reasons for not actively participating are the optional nature of the forums and, as indicated by many participants, the fact that they do not want to write to a large group of anonymous users [24]. These problems are addressed in this study in an Internet-based group guided self-help treatment in which small therapist-guided groups of participants start simultaneously, introduce themselves to each other, and then conjointly work their way through the Internet-based self-help guide. It should be noted that the Internet-based group treatment is different from group therapy in face-to-face settings as the main component of the intervention is a self-help program. Regarding group therapies for SAD, evidence suggests that the group situation may be too threatening for social phobics, resulting in individuals inverting or “shutting down” and gaining less in group settings than in individual settings [25]. In the Internet-based setting, the asynchronous, distant communication with other group members may not provoke overwhelming anxiety symptoms and allows participants to concentrate on the content of the treatment.

### Objective and research questions

The primary aim of this study is to evaluate whether the newly developed group guided self-help treatment for SAD is effective in reducing social anxiety symptoms when compared to a waiting-list control group and an individually guided self-help treatment. It is expected that the active intervention groups will be superior to the waiting-list control group with regard to primary social anxiety measures and secondary outcomes such as depression, general symptomatology, interpersonal problems and quality of life. It is further expected that the group guided self-help treatment will be superior to the individually guided self-help treatment in terms of adherence to treatment, treatment satisfaction and cost as estimated from the amount of therapist time required for each client.

## Methods/design

### Study design

This study is conducted as a randomized controlled trial. Participants are randomly assigned to either of the active conditions or the control condition. Main component of the active conditions is an internet-based self-help program, which will either include individual support by a psychologist or therapist-guided peer support in groups of six participants.

### Ethical approval

This study has been approved on 14/06/2013 by the Cantonal Ethics Committee Bern (ref. nr. KEK-BE: 062/13).

### Participants

A total of 150 fulfilling the diagnostic criteria of SAD are being recruited, with 60 participants assigned to each of the active conditions and 30 participants to the waiting-list control group. Participants are recruited in Switzerland, Austria and Germany through a study website and postings in Internet forums.

### Inclusion criteria

1 The patient is at least 18 years of age.

2 The patient provides a written informed consent.

3 The patient has access to a computer with internet connection.

4 The patient has sufficient German language skills to benefit from the program and provide usable data through questionnaires and interviews.

5 The patient exceeds pre-defined cut-off scores in one of the social anxiety measures.

6 The patient meets the diagnostic criteria for SAD according to the diagnostic telephone interview.

7 The patient agrees to undergo no other psychological treatment for the duration of the study. The patient agrees to undergo no other psychological treatment when joining the study (Patients are asked for report, if they do so later on while taking part in the study. In this case, this patients’ data would be excluded from evaluation.)

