### Randomization

After checking the inclusion criteria, a weighted randomization procedure is used in which 60 participants are assigned to each of the active treatment conditions and 30 participants to the waiting-list control group. The allocation list is produced by a computerized random number generator operated by an independent researcher and is unknown to the investigators.

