### Analysis

Intent-to-treat samples will be used to analyze data. The choice of statistical approach depends on the amount of missing data at post- and follow-up-assessment. In the case of less than 12% missing data, the Last Observation Carried Forward (LOCF) method will be applied to estimate effects. Then, the primary outcome will be computed with an analysis of covariance (ANCOVA), using the pre-scores as a covariate and the post-scores as the dependent variable.

If more than 12% of participants stop the treatment, we will use linear mixed models. This method is recommended for intent-to-treat-analyses with a high amount of dropouts due to its potential to reduce bias caused by missing data. The level of significance will be 5% (α = 0.05). Significance testing of the diagnostic status and clinically significant change will be conducted with chi-square tests. Regression analyses will be used to identify predictors of treatment outcome.

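### Excluding participants who take up other psychological treatment after randomisation contradicts the stated intent-to-treat analysis and can bias the arm comparisons

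*Protocol article*

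**What the plan says.** Three places in the protocol article bear on this.

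- **Inclusion criteria, item 7.** The first sentence reads "The patient agrees to undergo no other psychological treatment for the duration of the study". A second, nearly identical sentence refers to the time of joining. A parenthesis then adds "Patients are asked for report, if they do so later on while taking part in the study", and says that in this case the participant's "data would be excluded from evaluation".
- **Randomization.** "After checking the inclusion criteria, a weighted randomization procedure is used". Eligibility is therefore settled before allocation.
- **Analysis.** "Intent-to-treat samples will be used to analyze data". The section then gives two ways of dealing with incomplete data. One is "In the case of less than 12% missing data, the Last Observation Carried Forward (LOCF) method will be applied to estimate effects". The other is "If more than 12% of participants stop the treatment, we will use linear mixed models". It names no modified intent-to-treat set, no per-protocol set and no exception for participants who receive other treatment.

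**The concern.** Item 7 sits among the eligibility criteria, but its parenthesis acts as an analysis rule. It drops people who have already been randomised because of something that happens later, and an intent-to-treat analysis exists to avoid that.

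The event may be linked to arm and to outcome. According to the Procedure section, the waiting list gets the program 12 weeks later, while both active arms have weekly contact with a psychologist. Participants who are not improving may have more reason to look elsewhere. The event is also known only from the participant's own report, and reporting could differ between arms with and without regular contact.

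Timing adds to the problem. Assessment runs to six months after randomisation, but the primary outcomes are measured at 12 weeks. Read literally, a participant who starts other treatment in month five would lose a 12-week outcome that was already observed and that the other treatment could not have affected.

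At stake are the randomised basis of the comparisons and some of the planned power.

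**Working it through.** **1. The passages side by side.** Eligibility is checked, then participants are randomised, then the triggering event occurs during participation, then the data are left out. The rule therefore acts on randomised participants. The Analysis section says the intent-to-treat sample is analysed. Its provisions for incomplete data keep participants in the analysis, whereas item 7 takes them out. Nothing else in the article reconciles the two.

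**2. The plan's own sample size.** The Power section gives d = 0.35, α = 0.05, power 0.80 and 60 per active arm, using a pre-post correlation ρ whose value is not stated. Two-sided testing is assumed here.

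- Without a correlation: n = 2 × ((1.960 + 0.842)/0.35)² = 128.1, so 129 per arm.
- ANCOVA: n = 128.1 × (1 − ρ²). Setting n = 60 gives ρ = √(1 − 60/128.1) = 0.729.

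The figure of 60 is attainable but cannot be confirmed without ρ. The value 0.729 is used below.

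**3. Loss of power from smaller arms alone**, active versus active, d = 0.35 (exclusion rates assumed):

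| Excluded per arm | n per arm | Power |
|---|---|---|
| 0% | 60 | 0.80 |
| 5% | 57 | 0.78 |
| 10% | 54 | 0.76 |
| 15% | 51 | 0.73 |
| 20% | 48 | 0.71 |

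**4. Shift of the contrast.** Let p be the fraction excluded in an arm and D the mean outcome difference, in SD, between excluded and retained participants. The full-arm mean equals the retained mean plus p × D, so exclusion moves that arm's mean by p × D. The contrast moves by the difference between the two arms' products. Taking D = 0.5 in both arms (assumed):

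- Waiting list 20%, active 5%: 0.5 × 0.20 − 0.5 × 0.05 = 0.100 − 0.025 = 0.075 SD.
- Waiting list 10%, active 5%: 0.050 − 0.025 = 0.025 SD.
- Equal products in the two arms, or D = 0: no shift.

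Allocation is "60 participants assigned to each of the active conditions and 30 participants to the waiting-list control group", so 20% of the waiting list is 0.20 × 30 = 6 people and 5% of an active arm is 0.05 × 60 = 3. For scale, 0.075/0.35 = 0.21 of the smallest between-active-arm effect that the Power section treats as clinically relevant.

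**5. Simulation with ANCOVA.** There were 4,000 replicates with ρ = 0.729 and differences in baseline SD units. Except in the first row, the chance of exclusion rises with a worse baseline-adjusted post-score (logistic slope 2). All rates are assumed.

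| Scenario | True difference | Excluded | Estimate after exclusion | Rejection rate, all randomised → after exclusion |
|---|---|---|---|---|
| 60 vs 60, unrelated to outcome | 0 | 5% vs 15% | about 0 | 0.05 → 0.05 |
| 60 vs 60, related, equal | 0 | 5% vs 5% | about 0 | 0.05 → 0.05 |
| 60 vs 60, related | 0 | 5% vs 15% | 0.07 | 0.05 → 0.09 |
| 60 vs 60, related | 0 | 5% vs 20% | 0.11 | 0.05 → 0.13 |
| 60 vs 60, related | 0.35 | 5% vs 15% | 0.28 | 0.79 → 0.59 |
| 60 active vs 30 waiting list, related | 0.80 | 5% vs 20% | 0.69 | above 0.99 → 0.99 |
| 60 active vs 30 waiting list, related | 0.80 | 5% vs 30% | 0.63 | above 0.99 → 0.96 |

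The 0.80 stands in for the large difference that the Power section expects without giving a figure.

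**The case against.** The best defence is that harm is not demonstrated. The protocol gives no rate of outside treatment, no split by arm and no outcome difference. A reader might infer that the rule does bias the comparisons, or that it removes treatment failures from the active arms and the most distressed people from the waiting list. The documents do not support either statement. They support the 12-week delay for the waiting list and nothing further about who would seek other care. The simulation shows essentially no bias when exclusion is unrelated to outcome, or when it is related to outcome but equal in two arms with no true difference. For active versus waiting list, even the harsher scenarios leave power at 0.96 or above. For the two active arms, the documents give no particular reason why uptake should differ. All of this stands, and it limits the claim to one of possible bias.

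A reader might also infer that the damage could not be undone. That does not follow. Item 7 keeps data out of the evaluation but does not say that assessment stops, and the Procedure section has all three groups assessed at every time point. If the data are collected, they can be analysed.

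It could also be argued that only observations made after other treatment began are meant, in which case the participant would stay in the sample with later values missing. The wording does not say so, and the natural reading is the whole record. Even on the narrower reading, the missing values could be informative.

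Finally, the two sentences of item 7 might be called a self-contradiction. They can be read together, one giving what is agreed and the other when agreement is given. This is a point of wording without analytic consequence of its own.

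None of these arguments reconciles item 7 with the Analysis section.

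**Conclusion.** The point holds as a contradiction in the text: an exclusion triggered after randomisation stands beside an unqualified intent-to-treat statement. This does not depend on any assumed rate, and it is not a detail that an article may leave to an analysis plan, because both rules are stated and they conflict.

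The size of the consequence is unknown. Bias requires uptake of other treatment to be related to outcome and the pattern to differ between arms. Its direction is open. If poor responders leave mainly from the waiting list, the treatment effect is understated; if they leave mainly from one active arm, that arm looks better than it is. On the assumed inputs the shift is 0.025 to 0.075 SD in the simple calculation. That is small against a large effect over the waiting list, but not negligible against the 0.35 on which the comparison of the active arms is planned. The loss of analysed participants occurs whether or not there is bias.

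**What to change.** Remove the exclusion from the primary analysis. State in the Analysis section that all randomised participants are analysed in their allocated arm whether or not they receive other psychological treatment, that they continue to be assessed at 12 weeks and six months, and that the date and type of any other treatment are recorded. Report the analysis without these participants only as a labelled sensitivity analysis. As a matter of wording, reconcile the two sentences of item 7. None of this changes what participants are asked to agree to.

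The cost is about one sentence in the protocol and in the analysis plan. Reports of other treatment are already requested, so only date and type may need adding. The Trial status section shows recruitment still open (83 of a planned 150 in April 2014), so at that point the rule could be changed before analysis.

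The downside is that the primary estimate then includes any effect of outside treatment. The sensitivity analysis lets readers see how much the result depends on these participants, though it is itself open to the selection described above.

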### Exclusion criteria

1 The patient has active suicidal plans (according to the suicide item of the BDI or the diagnostic telephone interview). These individuals are referred to a local psychiatrist or psychotherapist.

2 The patient has a history of psychotic or bipolar disorders.

3 Prescribed medication for anxiety or depression only leads to exclusion if the dosage has been changed during the last month prior to the study.

### Randomization

After checking the inclusion criteria, a weighted randomization procedure is used in which 60 participants are assigned to each of the active treatment conditions and 30 participants to the waiting-list control group. The allocation list is produced by a computerized random number generator operated by an independent researcher and is unknown to the investigators.

### Description of the interventions

a) Internet-based individually guided self-help without peer support:

The main component of the 12-week treatment is a self-help program, which has been successfully evaluated in previous studies [15,23,26,27]. The theoretical background of this program is based on Clark & Wells’ well-established cognitive-behavioral treatment model [28]. The program contains eight text-based sessions, including several exercises (such as attention training) and diaries (e.g. diaries to identify and challenge dysfunctional assumptions). Participants are asked to work trough one session per week, repeat the exercises and fill in the diaries. One session can be completed in approximately 60 minutes. Table 1 shows an overview of the content. While working with the program, the participants receive individual support by psychologists via an integrated email function of the platform. The psychologists contact the participants on a weekly basis in order to provide structure and reinforce program use. The patients can use the email function to contact the psychologists whenever they want to. Supervision of the supporting psychologists is provided by the study direction. This intervention does not include any possibility of group-guided support (e.g. in a discussion forum).

b) Internet-based group guided self-help treatment:

Participants in the second active condition use the same internet-based self-help program as described above. In contrast, they will not be supported individually, but within groups of six participants. All members of one group start the intervention at the same time and use an integrated, protected discussion forum to communicate with each other under the guidance of a psychologist. At the beginning, the group members and the supporting professional introduce themselves. The group members are encouraged to share their experiences, problems and questions with each other. The messages posted in the forum are accessible to every group member and the psychologist, as well. Analogous to the first treatment condition, the psychologists contact the group on a weekly basis. The psychologists’ short messages aim at providing the group with structure and motivation.

The participants are asked to choose a pseudonym instead of their real name for the digital communication, so as to protect their privacy. The supporting psychologists supervise adherence to this guideline and will delete real names.

**Table 1 T1:** **Content of the internet-based self-help program for SAD**[29]

Session 1: Motivational enhancement	Reasons to initiate change, definition of goals, recording of difficult social situations
Session 2: Psychoeducation	Information on SAD and its maintaining processes such as negative beliefs, self-focused attention and safety behaviors
	Development of an individual model for SAD
Session 3: Cognitive Restructuring	Identification and modification of dysfunctional assumptions using a thought record
Session 4: Self focused attention	Various exercises to reduce self-focused attention, e.g. short behavioral experiments
Session 5: Behavioral experiments	Planning and implementation of in vivo exposures
Session 6: Summary and Repetition	Summary of the key elements of the treatment with emphasis on the importance of repeated practice (e.g. in vivo exposure)
Session 7: Healthy lifestyle and problem solving	Information on healthy lifestyle behavior (physical exercise and nutrition)
	Development of problem solving skills
Session 8: Relapse prevention	Strategies for maintaining the skills learned, preparation for possible relapse

